### mHealth Supplement: COVID Rehabilitation Mobile App

As part of this study, and at the request of our user representative, a mobile app was developed. The app has been named *My COVID Rehabilitation* (Norwegian: *Min COVID Rehabilitering*). Both groups will be invited to download the mobile app. The mobile app is a digital pamphlet with relevant information, including the possibility to make personal notes and goals based on activities from the 3 focus areas. Users will receive a daily reminder of their goals. After completing the activity, a simple digital reward is provided. The mobile app is available on the App Store and Google Play, and only the participant will have access to personal notes and goals in the mobile app on their phone. The mobile app has been developed in collaboration with user representatives, the multidisciplinary health care team at UNN, and system developers at Information and Communication Technology, Northern Norway Regional Health Authority. In the development process, feedback was given at several time points and adjustments made on both content, phrasing, and visual presentation.

### Explorative Outcomes

This trial is embedded in ordinary clinical care at UNN with the last author ([name]) as project leader. At the same time, the study is part of a national research collaboration called ReCover. Participants are therefore invited to participate in voluntary supplement investigations at baseline and at 6-month follow-up. Written informed consent, including the collection, storage, and use of participant data, is obtained at the first visit. Explorative investigations of immunological, inflammatory, and metabolic changes of markers in plasma/serum and whole blood RNA and EEG/MRI are done to explore changes in brain volume, density of white matter fiber tracts, and brain activity. The ReCover study will explore if immune profile and changes in the brain are modulated by the intervention. Details on these supplementary investigations will be provided in other articles from the ReCover research group.

### Statistical Analyses

#### Sample Size

Sample size justification was made in collaboration with a statistician. Due to the lack of studies with a similar design, we could not have completely precise estimates of the between-group difference in EQ-5D-5L index and standard deviation. We based our sample size estimation on a study by Espinoza-Bravo et al [37] that closely resembled ours. Espinoza-Bravo et al [37] compared 2 interventions consisting of home-based exercise with digital follow-ups in both groups. They found a mean difference between groups of (SD) 0.06 on EQ-5D-5L index and a standard deviation (SD) of 0.1 at the end of the intervention. There is no established minimal clinically significant difference (MCID) for the EQ-5D-5L index in long COVID [17]. However, for a respiratory condition (chronic obstructive pulmonary disease), the estimated MCID is 0.05 [60], and this has been used in previous research in long COVID [37]. In stroke rehabilitation, the MCID for the EQ-5D-5L index is found to be 0.10 [61]. In our study, we expect a higher mean difference (SD 0.07) in the EQ-5D-5L index between groups than in the study by Espinoza-Bravo et al [37] because we have a larger difference in treatment design. We also consider that the difference of 0.07 could be clinically significant and therefore based the sample size calculation on a mean difference of 0.07 and an SD of 0.1. We have a one-sided hypothesis where we assume that the intervention group will have a higher EQ-5D-5L index than the control group after 6 months. With a 15% (9/62) expected dropout, a power of 80%, and a *P* value of .05, the required sample size is estimated to be 31 participants in each group. The power estimation was run in SAS Enterprise Guide 8.3 using the POWER procedure. Other RCTs in populations with long COVID have demonstrated differences between groups with similar sample sizes [62,63].

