According to the WHO, patients with long COVID may experience worsening of symptoms following minimal cognitive, physical, emotional, and social activity, or activity that could previously be tolerated [24]. A result of this is often a behavioral challenge where patients exceed their own tolerance limit, followed by complete rest, an all-or-nothing pattern. Others may generally fear activity because it may lead to exacerbation of symptoms, also called fear-avoidance. Such patterns are often seen in CFS/ME [25]. Graded fixed incremental exercise therapy is debated in the literature because it might cause PEM, which is associated with poor health outcomes [26-29]. Pacing, on the other hand, is how to balance activities and rest to avoid exacerbation of symptoms, and thus not fixed incremental steps [24]. In patients with long COVID, individualized activity plans with education on pacing should therefore be provided. It is documented as beneficial to gradually introduce activity to restore patients to previous levels of activity, including daily routines [5,30]. Interventions that combine pacing and graded escalation of physical and cognitive activities are called graded activity [25]. A recent review (2023) found graded activity based on elements from CBT to be effective in reducing fatigue and improving physical functioning in CFS/ME [25].

Findings from previous studies indicate that long COVID is a complex condition that can be treated by a graded activity intervention. Daily routines and regular physical and cognitive exercise may be 3 important focus areas in this behavioral management of long COVID.

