#### Data Analyses

The analysis plan was made in collaboration with a statistician. The primary outcome, between-group difference in EQ-5D-5L index score at 6 months follow-up, will be analyzed by a statistician blinded to the intervention groups. Prior to statistical analysis, we will run an exploratory analysis of the outcome to check for data distribution and the presence of outliers, and to check for associations between the outcomes and covariates. To explore the effect of improved HRQoL, we will use linear models adjusted for baseline HRQoL, age of patients, and gender. The response variable in the model will be HRQoL at the 6-month follow-up. The linear model will be checked using common diagnostic tools (eg, distribution of residuals and influential observations). We will also run an exploratory analysis of the secondary outcomes. Next, because secondary outcomes will be measured repeatedly at 0, 3, 6, and 12 months, we will apply statistical models that are suitable for longitudinal data (eg, generalized estimating equation or mixed models class). Common model diagnostics will also be used for secondary outcomes.

Results for the primary outcome analysis were reported as linear regression coefficients with 95% confidence interval and *P* value. The standard cut-off of *P*<.05 will be used for statistical significance levels. We will evaluate if the difference is clinically and statistically significant. For secondary outcomes, we will report appropriate effect measures with 95% CIs.

For neurocognitive function, to facilitate comparison across cognitive domains, all scores will be converted to *z* scores (*z* = (x − μ)/σ). Each individual cognitive test score will be described by mean and SD, and the cutoff for cognitive impairment on any test or domain score will be set to 1 SD or less from the normative mean.

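### The trial is sized on a one-sided 5% test, but the primary result is to be judged by a 95% CI and P<.05 with no sidedness stated, so two decision rules stand side by side

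*Protocol article*

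**What the plan says.** Protocol article, Sample Size: the hypothesis is directional. "We have a one-sided hypothesis where we assume that the intervention group will have a higher EQ-5D-5L index than the control group" after 6 months. The authors "based the sample size calculation on a mean difference of 0.07 and an SD of 0.1", with 80% power, a P value of .05 and a "15% (9/62) expected dropout". On these terms "the required sample size is estimated to be 31 participants in each group".

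Protocol article, Data Analyses: the response is HRQoL at 6 months, in a linear model adjusted for baseline HRQoL, age and gender. Primary results are "reported as linear regression coefficients with 95% confidence interval" and P value, against a cut-off of P<.05 that the text calls standard. The authors will then judge whether the difference is both clinically and statistically significant. This section mentions neither a one-sided test nor a two-sided one, and neither a one-sided bound nor a 90% interval.

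**The concern.** A one-sided 5% test matches a one-sided 95% bound or, equivalently, one limit of a 90% interval. A 95% interval that excludes zero is a two-sided 5% test. The two sections therefore give two criteria for one primary outcome, and the article does not say which governs.

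Two things depend on the choice. The first is the false-positive rate for declaring the individual programme superior: 5% under the one-sided rule, 2.5% under the rule implied by the 95% CI. The second is the power, since 80% belongs to the one-sided rule. The trial is unblinded apart from the statistical evaluation, and its primary outcome is self-reported, so the criterion should not be left to be settled once the estimate is known.

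**Working it through.** **Inputs** (Sample Size section): difference δ = 0.07, SD σ = 0.1, α = 0.05, one-sided, power 80%, dropout 15%. Allocation is 1:1 (Study Setting). Power is from the noncentral t distribution with 2n − 2 degrees of freedom and noncentrality δ / (σ√(2/n)).

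**1. The plan's own figure, one-sided 5%.**
- With n = 26 per arm, SE = 0.1 × √(2/26) = 0.0277 and noncentrality = 0.07/0.0277 = 2.52. The critical t on 50 df is 1.676, and power is 80.1%.
- Dropout: 26/0.85 = 30.6, rounded up to 31 per arm, 62 in total. The stated figure reproduces.

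**2. The same inputs, two-sided 5%.** The critical t on 50 df is 2.009.

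| Evaluable per arm | Two-sided power |
|---|---|
| 26 | 69.7% |
| 27 | 71.4% |
| 31 (no dropout) | 77.4% |
| 34 | 81.2% |

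The first n that reaches 80% is 34 by the t calculation (33 by the normal approximation). After dropout that is 34/0.85 = 40 (or 33/0.85 = 38.8, so 39) per arm. A two-sided calculation on these inputs therefore does not yield 31.

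**3. Where the two rules disagree (unadjusted, 26 per arm).**
- Smallest difference significant one-sided: 1.676 × 0.0277 = 0.046.
- Smallest difference whose 95% CI excludes zero: 2.009 × 0.0277 = 0.056.
- The band from 0.046 to 0.056 contains 0.05, the MCID for chronic obstructive pulmonary disease that the Sample Size section says has been used in long COVID. At exactly 0.05, t = 0.05/0.0277 = 1.80 and the one-sided P is 0.039, while the 95% CI is 0.05 ± 0.056, that is −0.006 to 0.106.
- If the true difference is 0.07, the chance of landing where the rules disagree is about 80.1% − 69.7% = 10.4%.

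**4. The planned adjusted model.** Adjustment for baseline reduces the residual SD to about σ√(1 − r²), where r is the correlation between baseline and 6 months. The article gives no r, so the values below are assumptions (26 per arm, two-sided 5%; age and gender ignored).

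| r | Residual SD | Two-sided power | Band of disagreement |
|---|---|---|---|
| 0 | 0.100 | 70% | 0.046–0.056 |
| 0.3 | 0.095 | 74% | 0.044–0.053 |
| 0.47 | 0.088 | 80% | 0.041–0.049 |
| 0.5 | 0.087 | 82% | 0.040–0.048 |
| 0.7 | 0.071 | 93% | 0.033–0.040 |

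Adjustment can recover the power. It moves and narrows the band but does not remove it.

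**The case against.** The strongest reply is that the plan can be read as consistent. The Sample Size section declares a one-sided hypothesis, and the Data Analyses section never says two-sided. The P value may be meant as one-sided, with the 95% CI given for estimation only. On that reading 80% is the correct power. This stands as far as it goes: the two-sided rule is inferred from the interval and from the description of the cut-off as standard. It does not reconcile the text, because the interval reported would still not match the test, and a reader could call the same result positive or inconclusive.

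A reader might also infer that the trial is underpowered at 70%. The article does not support that. The 70% is for an unadjusted comparison, whereas the primary model adjusts for baseline. Whether two-sided power falls short depends on a correlation the article does not give. Equally, the article does not claim that gain.

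A further tempting reading is that a one-sided test is unsuitable because the protocol itself warns of harm: "Graded fixed incremental exercise therapy is debated in the literature because it might cause PEM" (Treatment Content). That sentence concerns fixed increments, which the same section contrasts with pacing. The Study Intervention section describes a combination of pacing and graded escalation, so the warning is not about this intervention. The reported coefficient and 95% CI would also show a worsening, and adverse events are recorded. The point does not rest on this argument.

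Finally, the mismatch matters only for results within a narrow band, and the CI will be published in any case. That limits the consequence, but the band lies close to the differences the authors regard as clinically relevant.

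**Conclusion.** The point holds as an inconsistency between the design and analysis sections. It is not an arithmetic error: 31 per arm is right for a one-sided 5% test with 15% dropout. As written, the article carries two success criteria, which disagree for unadjusted observed differences of about 0.046 to 0.056 and which differ by a factor of two in the false-positive rate for superiority. If the rule implied by the 95% CI governs, power on the stated inputs is about 70% unadjusted (77% with no dropout), and 80% or more under the adjusted model only if the assumed correlation is about 0.47 or higher. All figures rest on the article's difference of 0.07 and SD of 0.1. A full protocol or SAP that is not shown may state the sidedness, but the mismatch in this text would remain.

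**What to change.** Before unblinding, state one decision rule for the primary comparison, with its matching interval, in both sections.

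- **Preferred:** a two-sided test at 5%, matching the 95% CI already promised. Restate the power as about 70% for an unadjusted comparison of 26 per arm, and 80% or more under the baseline-adjusted model only if the correlation between baseline and 6 months is about 0.47 or higher.
- **If the one-sided 5% test is kept:** say so in the Data Analyses section, report the matching one-sided bound or 90% CI, and acknowledge that the one-sided error rate is 5%.

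The cost is a few sentences and, under the preferred option, a less favourable statement of power. Recruitment of 62 is complete; no extra patients and no change to conduct are needed.

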#### Data Analyses

The analysis plan was made in collaboration with a statistician. The primary outcome, between-group difference in EQ-5D-5L index score at 6 months follow-up, will be analyzed by a statistician blinded to the intervention groups. Prior to statistical analysis, we will run an exploratory analysis of the outcome to check for data distribution and the presence of outliers, and to check for associations between the outcomes and covariates. To explore the effect of improved HRQoL, we will use linear models adjusted for baseline HRQoL, age of patients, and gender. The response variable in the model will be HRQoL at the 6-month follow-up. The linear model will be checked using common diagnostic tools (eg, distribution of residuals and influential observations). We will also run an exploratory analysis of the secondary outcomes. Next, because secondary outcomes will be measured repeatedly at 0, 3, 6, and 12 months, we will apply statistical models that are suitable for longitudinal data (eg, generalized estimating equation or mixed models class). Common model diagnostics will also be used for secondary outcomes.

Results for the primary outcome analysis were reported as linear regression coefficients with 95% confidence interval and *P* value. The standard cut-off of *P*<.05 will be used for statistical significance levels. We will evaluate if the difference is clinically and statistically significant. For secondary outcomes, we will report appropriate effect measures with 95% CIs.

For neurocognitive function, to facilitate comparison across cognitive domains, all scores will be converted to *z* scores (*z* = (x − μ)/σ). Each individual cognitive test score will be described by mean and SD, and the cutoff for cognitive impairment on any test or domain score will be set to 1 SD or less from the normative mean.

We will analyze significant between-group differences in cognitive domains at baseline to ensure comparability between the intervention and the control groups. We will also examine the mean changes in the 4 cognitive domains by calculating each participant’s average change in z-scores from T1 to T2 for each domain. These change scores are then compared between the intervention and control groups using significance testing and effect sizes [partial eta-squared (η²)]. Additionally, we will compute the Reliable Change Index (RCI) for each participant in both groups to categorize individual performance as stable, deteriorating, or improving based on clinically significant individual changes defined by the RCI. The RCI will be calculated using test-retest reliability estimates from published, normative samples [64].

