### Randomization

Participants will be block randomized with the computer program Research Electronic Data Capture (REDCap) either to the intervention group (n=31) or standard treatment group (n=31), presented in Figure 1.

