### Neurocognitive Functioning

A comprehensive neuropsychological assessment will be conducted at baseline and repeated at 6 months to evaluate 4 key cognitive domains. The following measures from standardized tests will be used to measure aspects of the 4 selected cognitive domains.

Episodic memory: the average score from the total number of correct words recalled in the delayed recall trial of the Rey Auditory Verbal Learning Test [45,46] and the Rey Complex Figure Test [47].Working memory: average score from the Letter-number-sequencing and Spatial Span subtests of the Wechsler Memory Scale-III [48].Executive functions: average completion time for the trial 1-5 of the Trail Making Test and the Inhibition trial of the Color-Word Interference Test, both from the Delis-Kaplan Executive Function System [49,50].Processing speed: average reaction time from the Conners Continuous Performance Test, 3rd edition [51].

Raw test scores are standardized using age-corrected published population norms. When available, published normative data from Scandinavian populations are prioritized. Scores will be reversed where necessary (reaction time) to ensure that higher scores consistently indicate better performance. Each assessment session will last 90 minutes, and the tests will be administered by a psychologist or trained health care personnel under supervision.

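### Baseline significance tests cannot establish that the arms are comparable on cognition; adjusting each cognitive comparison for its own baseline score would deal with imbalance directly and gain precision

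*Protocol article*

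**What the plan says.** Cognition is a secondary outcome with two measurements (Neurocognitive Functioning): "A comprehensive neuropsychological assessment will be conducted at baseline and repeated at 6 months to evaluate 4 key cognitive domains". The last paragraph of Data Analyses sets out its between-arm analysis in two steps. First: "We will analyze significant between-group differences in cognitive domains at baseline to ensure comparability between the intervention and the control groups". Then each participant's change in z score from the first to the second assessment is taken for each domain, and "These change scores are then compared between the intervention and control groups using significance testing and effect sizes", the effect size being partial eta-squared. No covariate is named, and nothing is said about what follows if a baseline test is or is not significant.

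The same section handles the primary outcome differently: a linear model for the 6-month EQ-5D-5L index with its baseline value, age and gender as covariates. It also plans longitudinal models for secondary outcomes, on the ground that these are measured at 0, 3, 6 and 12 months. Cognition is measured only at 0 and 6 months, so the dedicated cognitive paragraph is the one that most naturally governs it.

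On allocation, the Randomization section says: "Participants will be block randomized with the computer program Research Electronic Data Capture (REDCap", with 31 participants per arm.

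**The concern.** The stated purpose and the stated method do not fit together. If allocation was sound, the null hypothesis of a baseline test is true by design, so a significant result reflects chance. A non-significant result at this sample size is compatible with sizeable observed differences. What matters for the outcome comparison is how large the imbalance is and how strongly baseline predicts the 6-month score, and a P value measures neither.

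The comparison that follows does not fully absorb an imbalance. A change score subtracts the whole baseline difference, whereas only a fraction of it (the baseline–retest correlation) is expected to persist. The remainder appears as an apparent difference in change, through regression to the mean. At stake are the precision of the cognitive results and how they read if the arms happen to start apart. The article presents neuropsychological function as one of the contributions of this trial.

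**Working it through.** **Inputs from the article**
- 31 per arm (Randomization, Sample Size); 15% expected dropout (Sample Size).
- Four domains, measured at 0 and 6 months (Neurocognitive Functioning).
- Significance level (Data Analyses): "The standard cut-off of *P*<.05 will be used for statistical significance levels".

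**Assumptions**
- Baseline tests are two-sided, since comparability has no direction.
- The baseline–retest correlation rho is not given; 0.5 to 0.9 is shown.
- SDs are equal in both arms and at both times. Differences are in units of that SD. No treatment effect.

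**The article's own figure.** The sample size was "based the sample size calculation on a mean difference of 0.07 and an SD of 0.1", one-sided .05, 80% power. Then 2 × (1.645 + 0.842)² / 0.7² = 25.2, so 26 per arm; 26 / 0.85 = 30.6, so 31. This matches. About 26 per arm would remain at 6 months.

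**What a baseline test can flag.** Smallest significant difference = t(0.975, 2n−2) × √(2/n).
- n = 31: 2.000 × 0.254 = 0.51 SD.
- n = 26 (if restricted to completers): 2.009 × 0.277 = 0.56 SD.

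By chance alone at n = 31, the observed difference in a given domain exceeds 0.3 SD in about 24% of trials and 0.4 SD in about 11.5%. About 7% fall between 0.4 SD and the 0.51 threshold.

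**Chance significance.** 1 − 0.95⁴ = 0.185 for four independent tests. Cognitive domains are likely to be positively correlated, so this is best read as a ceiling.

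**Change score against baseline adjustment.** Given an observed baseline difference d, the expected 6-month difference is rho × d. The expected difference in change is therefore rho × d − d = −(1 − rho) × d, which favours the arm that started lower. The variance ratio of change score to adjusted analysis is 2(1 − rho) / (1 − rho²) = 2 / (1 + rho), ignoring the small cost of estimating the slope.

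The conditional type I error below compares the shifted estimate, with SE √(1 − rho²) × √(2/n), against the change-score critical value 1.96 × √(2(1 − rho)) × √(2/n). For d = 0.4, rho = 0.7, n = 31: shift 0.12, critical value 0.386, conditional SE 0.181, giving 7.4%.

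| rho (assumed) | Variance ratio | Shift at d = 0.4 SD | Conditional type I error, d = 0.4, n = 31 |
|---|---|---|---|
| 0.5 | 1.33 | 0.20 SD | 8.9% |
| 0.7 | 1.18 | 0.12 SD | 7.4% |
| 0.8 | 1.11 | 0.08 SD | 6.6% |
| 0.9 | 1.05 | 0.04 SD | 5.8% |

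**Simulation check** (60,000 trials, 26 per arm, rho 0.5 / 0.7 / 0.8). Over all randomisations the change-score test rejects in 5.0% / 4.8% / 5.1% of trials, so its level holds. About 23% of trials have an observed difference above 0.3 SD that is not significant. Within these, the change-score contrast is shifted by 0.20 / 0.12 / 0.08 SD and rejects in 8.0% / 6.6% / 6.2%. The baseline-adjusted analysis is shifted by about 0.00 and rejects in 5.0% / 4.7% / 5.0%.

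**The case against.** Several points on the other side stand.

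- **No decision rule.** A reader might infer that imbalances below the threshold will be declared acceptable, or that a significant test will trigger later adjustment. The article attaches no consequence to either result. As written, the tests are a preliminary that alters no estimate, and deleting them alone would change nothing in the comparison.
- **Not the only protection.** A reader might take the tests as the sole safeguard for cognition. Randomisation is the main one, and the change score itself removes much of an imbalance: at rho 0.7, 0.4 SD shrinks to 0.12 SD.
- **No bias in the usual sense.** A reader might conclude that the change-score test is invalid. Over all randomisations it is unbiased and holds its level. The shift is conditional on an imbalance having been observed; the unconditional cost is precision.
- **A significant test is not always a false alarm.** That presumes sound allocation and baseline testing not influenced by it. The trial is open apart from the statistical evaluation, and the text shown does not say whether cognitive testing precedes allocation. Even as an allocation check, though, the test is weak: at 31 per arm it would detect a true 0.4 SD difference with 34% probability.
- **Covariates may be specified elsewhere.** Partial eta-squared is compatible with a covariate model, and a condensed article may leave a covariate list to the full plan. For that reason the point rests on what is written: a purpose that the stated method cannot serve, and a described contrast of change scores.
- **Size depends on rho.** Three of the four domains average two tests or trials, which tends to raise rho. At 0.9 the gain is small.

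**Conclusion.** The point holds in a limited form. Significance tests of baseline cognition cannot establish comparability: at 31 per arm they are silent below about 0.51 SD, and under sound randomisation they produce at least one significant domain in up to 18.5% of trials. The change-score comparison, as described, is valid on average but less precise than an analysis adjusted for baseline, by 11% to 33% in variance for rho between 0.8 and 0.5 and about 5% at 0.9. If an imbalance occurs, the comparison leaves (1 − rho) × d in favour of the arm that started lower.

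The documents do not support the stronger claims that the tests act as a gate on the analysis or that the overall type I error is inflated. The sizes rest on assumed correlations, two-sided baseline tests and equal SDs. Cognition is a secondary outcome, and the primary analysis already includes its baseline value. The change is worth making because it is free, not because the trial's main conclusion depends on it.

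**What to change.** Compare the 6-month z score of each cognitive domain between arms in a linear model that includes that domain's baseline score, whatever imbalance is observed. Using the change score as the response with the same covariate gives the same treatment estimate, so the planned change-score presentation can stay. Partial eta-squared can be taken from this model.

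Replace the baseline significance tests with a table of baseline domain scores by arm (mean and SD).

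The cost is two sentences in the analysis section, ideally settled before the cognitive data are analysed by arm. Baseline scores are already collected; no visit, sample size or primary-analysis change is needed.

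### The four cognitive domains are compared between arms by change score with no baseline covariate; adjusting for the baseline score already collected would usually be more precise, at no cost

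*Protocol article*

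**What the plan says.** The article's Neurocognitive Functioning section sets two assessments: "A comprehensive neuropsychological assessment will be conducted at baseline and repeated at 6 months to evaluate 4 key cognitive domains". On scoring it says: "Raw test scores are standardized using age-corrected published population norms".

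Data Analyses then gives cognition its own method. The analysis variable comes from "calculating each participant’s average change in z-scores from T1 to T2 for each domain". For the comparison between arms: "These change scores are then compared between the intervention and control groups using significance testing and effect sizes". The effect size named is partial eta-squared, and no covariate is mentioned. A step on baseline comes before this: "We will analyze significant between-group differences in cognitive domains at baseline to ensure comparability between the intervention and the control groups". Nothing is said about what follows if such a difference is found.

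Two other analyses in the same section serve as comparison. For the primary outcome, "we will use linear models adjusted for baseline HRQoL, age of patients, and gender", with the 6-month value as the response. For the other secondary outcomes, "because secondary outcomes will be measured repeatedly at 0, 3, 6, and 12 months, we will apply statistical models that are suitable for longitudinal data". Cognition is measured only at 0 and 6 months, so that sentence does not clearly cover it.

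**The concern.** Cognition has the same structure as the primary outcome: one baseline value and one 6-month value in the same randomized participants. The primary outcome gets a baseline-adjusted model and cognition gets a plain comparison of change, with no reason given for the difference.

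A change score is equivalent to adjusting for baseline with the slope fixed at 1. When the true slope is below 1, the subtraction removes too much. The result is usually a noisier estimate, and one that depends on whatever baseline difference chance produced. The article presents standardized neuropsychological testing as a complement to self-report, and the trial has only 31 participants per arm, so precision that costs nothing is worth having.

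**Working it through.** **Inputs.** From the Sample Size section: difference 0.07, SD 0.1, one-sided 0.05, 80% power, 15% dropout, 31 per arm. The documents give no variance, power or correlation for the cognitive domains. Assumed here: rho from 0.5 to 0.9, equal variance at both visits, and the 15% dropout applied to cognitive testing.

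**The plan's own figure.** n per arm = 2(1.645 + 0.842)² / (0.07/0.1)² = 25.2, rounded up to 26. Then 26/0.85 = 30.6, rounded up to 31. The stated 31 reproduces and is not affected by this point. It supplies the 26 completers per arm used below.

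**Precision.** With outcome SD σ and n per arm:

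- Variance of the change-score contrast = 2σ²(1-rho) × 2/n.
- Variance of the baseline-adjusted contrast = σ²(1-rho²) × 2/n × (1 + 1/48). The last factor is the small-sample cost of estimating one slope with 52 participants.
- Ratio, adjusted to change = (1+rho)/2 × (1 + 1/48).

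If age and gender are added as well, the last factor becomes about 1 + 3/46, taking both as uninformative once scores are age-normed.

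| Assumed rho | (1+rho)/2 | Baseline only | Baseline, age, gender | CI narrower by (baseline only) |
|---|---|---|---|---|
| 0.5 | 0.75 | 0.77 | 0.80 | 12.5% |
| 0.7 | 0.85 | 0.87 | 0.91 | 6.8% |
| 0.8 | 0.90 | 0.92 | 0.96 | 4.1% |
| 0.9 | 0.95 | 0.97 | 1.01 | 1.5% |

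In power terms, where the baseline-only model has 80% power (two-sided 0.05), the change-score test has about 69%, 74%, 77% and 79% at these four correlations.

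**Sensitivity to chance imbalance.** Given a baseline difference d in SD units, the change-score estimate shifts by -(1-rho)d and the adjusted estimate by about 0. With 26 per arm, d has a standard deviation of sqrt(2/26) = 0.28. For d = 0.3 the shift is -0.15, -0.09, -0.06 and -0.03 SD at rho 0.5, 0.7, 0.8 and 0.9.

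**Simulation check** (26 per arm, 20,000 runs). The slope of the change-score estimate on d was -0.48, -0.30 and -0.20 at rho 0.5, 0.7 and 0.8. For the adjusted estimate it was 0.015 or less in size. Both estimators averaged zero under no effect.

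**Does the baseline test protect?** With 31 per arm the standard error of a baseline difference is sqrt(2/31) = 0.25 SD, so only differences above about 0.5 SD reach P<.05. A difference of 0.4 SD (0.4/0.254 = 1.57 standard errors, P about .12) would pass as comparable. It would still move the change-score estimate by -0.20 SD at rho 0.5 or -0.12 SD at rho 0.7.

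**The case against.** The strongest defence is that the planned test is sound: over randomizations the change-score contrast is unbiased and its error rate holds. That stands. A reader might infer that baseline imbalance is simply left in the treatment effect, or that the comparison is biased. Neither is so. The subtraction removes the imbalance and overshoots by a fraction (1-rho), with opposite sign. This is conditional on the imbalance that happened to occur.

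A reader might also infer that adjustment wins at any correlation below 1. That is a large-sample statement assuming equal variances. With 26 per arm and three covariates, the advantage is gone at rho 0.9, as the table shows. Rho is not in the documents, so the gain cannot be fixed more closely.

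Partial eta-squared has no sign, and it is tempting to say the report could not show which arm did better. The documents do not support that. Mean changes per domain will be examined, and Data Analyses promises suitable effect measures with 95% CIs for secondary outcomes.

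Finally, the article names no specific test, and partial eta-squared belongs to the ANOVA/ANCOVA family, so the full protocol, which is not shown, may contain a covariate. That is possible. The article, however, fixes both the variable and the comparison and mentions no adjustment, whereas it lists the covariates for the primary outcome.

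**Conclusion.** The point holds as one of efficiency and of conditional sensitivity to imbalance, not of validity. As written, the cognitive comparison makes no use of the baseline score beyond subtracting it. A baseline-adjusted model would usually be more precise: a variance ratio of 0.77 at rho 0.5, rising to 0.97 at rho 0.9. It would also remove the -(1-rho)d shift. These sizes rest on an assumed rho, equal variances at the two visits and 26 completers per arm. At very high correlation the gain is negligible. The baseline significance tests do not fill the gap, because they miss imbalances that matter and prompt no action. The outcome is secondary, so neither the sample size nor the primary conclusion is affected.

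**What to change.** Before the cognitive data are analysed, specify for each domain a linear model of the 6-month z-score on arm and the same-domain baseline z-score. Report the adjusted mean difference in z units with its 95% CI as the between-group result.

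Age and gender may be added for consistency with the primary model. This costs a few degrees of freedom, and age may add little because the scores are already age-normed. Settle the covariates in advance either way.

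Keep mean change by arm and partial eta-squared as description, and leave the Reliable Change Index as an individual classification. Drop the baseline significance tests, or state that they are descriptive and do not decide the model.

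The cost is a change of wording in the analysis plan. No new data, visits or participants are needed.
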